## Abstract

**Background:**

Osteoarthritis often results in prolonged periods of reduced physical activity and is associated with adverse health outcomes, including increased risk of cardiovascular and metabolic diseases. Exercise interventions for patients on the waiting list for arthroplasty can reduce the risk of long-term adverse outcomes by increasing activity levels. However, uptake and ongoing positive rates of physical activity in this population are low and the impact of pre-operative behaviour counselling on exercise is not known.

**Method/design:**

The exercise and behaviour change counselling (ENHANCE) trial is a two-arm assessor-blind randomised controlled trial to assess the effectiveness of a 12-week exercise intervention designed to improve long-term physical activity and functional abilities for people awaiting arthroplasty. Participants on the waiting list for hip and knee arthroplasty are recruited from one clinical site in Australia. After collection of baseline data, participants are randomised to either an intervention or control group. The control group receive usual care, as recommended by evidence-based guidelines. The intervention group receive an individualised programme of exercises and counselling sessions. The 12-week exercise programme integrates multiple elements, including up to five in-person counselling sessions, supported by written materials. Participants are encouraged to seek social support among their friends and self-monitor their physical activity. The primary outcome is physical activity (daily step count and percentage of day spent in sedentary activities). Secondary outcomes include pain ratings, physical function, psychosocial factors and changes in clinical markers linked with potential common chronic diseases (diabetes and cardiovascular disease). All outcomes are assessed at baseline and 26 weeks later and again at 26 weeks post-surgery.

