## Background

Osteoarthritis (OA) is a common musculoskeletal problem, which affects over 40% of adults over the age of 70 years [1] and is associated with substantial pain and disability [2]. Patients with advanced OA of the hip or knee are often referred for surgery to replace the affected joints. Internationally, the waiting time for surgery varies from 6 to 12 months [3]. Due to pain, physical activity levels in patients with OA are substantially lower than levels in non-arthritic older people [4]. The prolonged periods of reduced physical activity during the wait for elective surgery significantly increase the risk of developing other major health problems, such as cardiovascular and metabolic diseases [5]. Inactivity may exacerbate physical impairments, such as muscle weakness, resulting in an increased rate of functional decline [6] and reduced rate of recovery post-surgery. In contrast, substantial research supports the benefits of regular physical activity in the prevention and treatment of chronic medical conditions including OA [7, 8] at all stages of the disease.

Previous research has largely concentrated on the effects of pre-operative exercise on post-operative pain and mobility [9]. Despite small improvements of 10% in physical activity after joint replacement, activity remains much lower than in healthy people [10]. The reason for this is unknown but may be because patients’ adherence to exercise tends to drop over time [11] and clinicians often do not appreciate and promote exercise as a treatment option [12]. Consequently, the immediate small positive benefits in pain and mobility are not sustained, as participants are not adequately supported to maintain exercise levels once the intervention finishes. An individualised intervention programme with a counselling component may address the challenge of achieving prolonged increases in physical activity for patients with OA.

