Physical activity interventions based on social psychological theory are more effective than atheoretical ones in promoting health-protective behaviour [13]. In addition, interventions are more cost-effective when they have theoretically devised approaches and clearly measurable constructs. A theoretical basis for the intervention components and inclusion of key psychological measures based on theory can demonstrate *how* the intervention works, highlighting the processes by which behaviour change occurs [14]. The Health Action Process Approach (HAPA) [15] stipulates a dual-phase approach to action: a *motivational* phase (i.e. outcome expectancy, risk perception, action self-efficacy and intention) and a *volitional* phase (i.e. maintenance self-efficacy, recovery self-efficacy, action planning, coping planning and action control). According to HAPA, intention is a necessary but insufficient condition for action initiation and persistence. People also need to identify effective volitional self-regulatory strategies to enact their intentions and prevent relapse. The effectiveness of HAPA-based interventions has been demonstrated in multiple populations and contexts and across multiple health behaviours [15–21]. The use of this framework to promote physical activity in people with OA does not appear in the literature. However, HAPA has recently been used to identify six physical activity attributes that are most salient to adults with knee OA [22], which supports this framework in this population.

This report describes the methodology of the ENHANCE trial, a randomised controlled trial to test the effectiveness of the ENHANCE programme for a usual care control group. This study seeks to test the hypothesis that the combination of a targeted exercise prescription with behaviour change counselling based on HAPA will be more effective than usual care in increasing the number of daily steps at all-time points after intervention. Concurrently less pain, improved function and reduced metabolic and cardiovascular risks factors will be recorded.

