### Inclusion criteria

To be eligible to participate in the trial, patients have to meet the following criteria: new and existing patients on the surgery waiting list (<6 months on list), aged 80 years and younger (due to older people being less mobile and more sedentary and having more comorbidities and poorer cognition), able to read and understand English, willing to participate in a 12-week exercise intervention and provide informed consent.

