### Usual care

Participants in the control group receive a generic information brochure at their baseline assessment point, *Arthritis (osteoarthritis) and exercise*, produced by Exercise is Medicine Australia [24]. Otherwise, participants allocated to usual care receive their concomitant care while they are on the surgical waiting list, attending for ENHANCE assessments at 6 months after baseline and at 6 months after their surgery.

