### Randomisation

After completing all baseline data collection measures, participants are randomised to either the intervention group or the control group. Participants in the intervention group receive evidence-based physical activity guidelines supervised by an AEP for the 12 weeks. In addition, those in the intervention group receive an instructor-developed exercise booklet, along with innovative counselling classes five times directly after their exercise session. Participants in the control group will receive an information sheet with general advice on the benefits of physical activity for adults with OA. Participants in either group may receive relevant concomitant care and interventions.

The randomisation schedule has been prepared by a researcher independent of the research project using a computer-generated random number table. To conceal randomisation, the independent researcher has prepared consecutively numbered, sealed, opaque envelopes, which are kept in a locked location. As ENHANCE is an exercise intervention, blinding of the participants and the researchers who conduct the exercise sessions is not possible. Outcome assessors will not be involved in the delivery of the intervention and will be blinded to group allocations.

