### Primary outcome measure

The primary outcome measure is daily physical activity (daily step count and percentage of day spent in sedentary activities). Participants will wear an activity monitor (activePAL™) for seven consecutive days. Data from the device will be recorded and uploaded to a computer. These data will be averaged over the 7 days of activity to calculate a daily step count. The percentage of the day spent in sedentary activities will also be recorded. This measure will be taken upon entry to the study (test 1), and at approximately 6 months (test 2), and then at 6 months after surgery (test 3).

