### Data analysis

Differences in primary and secondary outcomes between groups will be compared using an intention-to-treat analysis. Once a participant is randomised to a study group, they will be considered a trial participant and analysed according to their allocated group, regardless of missing data for follow-ups or the amount of intervention received. Bivariate relationships will be tested with Pearson or Spearman correlations, independent *t*-tests or Mann–Whitney *U* tests (to examine relationships between the dependent variables and the independent variables) or chi squared tests for categorical variables. Each primary and secondary outcome will be analysed using a two-way repeated-measures analysis of covariance (ANCOVA) to determine differences between groups (exercise versus usual care) and between time points (test 1, test 2 and test 3). In addition, effects of the intervention targeting the psychological HAPA-based constructs on regular exercise is tested along with the key processes (mediation) involved. Data will be analysed with a linear mixed model with condition as between-participants effects and time points as within-participants effects. A path analysis will be used to determine mediation effects. Data analysis will be performed using statistical software STATA (STATA 13, Stata Corp, College Station, TX, USA) and Mplus. Statistical significance is set at *p* < 0.05 for all analyses.

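### Test 3 is defined only for participants who have surgery, so the intention-to-treat promise cannot be met at that time point; test 2 is not affected by this definition

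*Protocol article*

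**What the plan says.** The abstract of the protocol article sets the schedule: "All outcomes are assessed at baseline and 26 weeks later and again at 26 weeks post-surgery". The Primary outcome measure section repeats it for step count and sedentary time: "at approximately 6 months (test 2), and then at 6 months after surgery (test 3". The Usual care section gives controls the same rule, "attending for ENHANCE assessments at 6 months after baseline and at 6 months after their surgery". The Assessment and Secondary outcomes sections agree.

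Randomisation comes earlier, while participants are still waiting for their operation: "After completing all baseline data collection measures, participants are randomised to either the intervention group or the control group".

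The Background states the hypothesis that the programme "will be more effective than usual care in increasing the number of daily steps at all-time points after intervention", and it also expects less pain and better function. The Data analysis section promises intention-to-treat for primary and secondary outcomes. Every randomised participant is to be analysed in the allocated group, "regardless of missing data for follow-ups or the amount of intervention received". The same section puts tests 1, 2 and 3 together in a two-way repeated-measures ANCOVA. It also names a linear mixed model, without making clear which outcomes that model covers.

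Nowhere does the article give a test 3 date for someone whose operation is cancelled, declined or not done within the trial. Nor does it say that the test 3 comparison is meant only for operated participants.

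**The concern.** Tests 1 and 2 exist for everyone randomised. Test 3 exists only once a later event, surgery, has happened. For a participant who is never operated on, the test 3 value is undefined rather than merely unrecorded. Keeping the allocated label on those who were operated on does not bring back the randomised comparison, because each arm has been filtered after randomisation.

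The filter need not act equally in both arms. The programme targets pain and function, which plausibly bear on whether and when a person goes ahead with joint replacement. If the arms differ in who is operated on, the test 3 contrast mixes the effect of the programme with a difference in case mix. Because the hypothesis covers all later time points and test 3 is a primary-outcome visit, one part of the primary claim is exposed.

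**Working it through.** **1. What each visit is timed from**

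| Visit | Timed from | Defined for |
|---|---|---|
| Test 1 | entry, before randomisation | everyone |
| Test 2 | baseline, 26 weeks | everyone |
| Test 3 | surgery, 26 weeks | operated participants only |

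The intention-to-treat promise and the all-time-points hypothesis both cover the third row, but that row does not exist for a participant without surgery.

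**2. Spread of test 3 in time.** The Background says "Internationally, the waiting time for surgery varies from 6 to 12 months", and eligibility requires less than 6 months already on the list. If that international range held at this site (an assumption), the remaining wait at entry would run from just over 6 − 6 = 0 to 12 − 0 = 12 months. Test 3 would then fall from just over 0 + 6 = 6 to 12 + 6 = 18 months after entry. Time from randomisation to test 3 is therefore itself an outcome of the waiting process.

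**3. The plan's own sample size.** The Sample size section gives 50 per group, 1200 steps, alpha 0.05 and power 0.80, with no SD. Solving back (two-sided, normal approximation):

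SD = 1200 × √(50/2) / (1.960 + 0.842) = 6000 / 2.802 ≈ 2142 steps.

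A one-sided test would imply about 2413. The 50 cannot be reproduced independently; 2142 is used below as the implied value. Recruitment of 110 is 100 × 1.10, and its 10% allowance is for withdrawal only.

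**4. Bias at test 3, simple form.** Let u be the share of an arm not operated on, and gap the mean steps of non-operated minus operated participants, taken as equal in both arms. Since the overall mean = operated mean + u × gap, the operated mean is the overall mean − u × gap, and

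shift in contrast = −(u_intervention − u_control) × gap.

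The documents give neither u nor gap. Assumed values:

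- u = 0.20 and 0.10, gap = +1000 to +2000: shift = −0.10 × 1000 to −0.10 × 2000 = −100 to −200 steps (8% to 17% of 1200).
- Same u, gap = −1000 to −2000 (non-operated participants walk less, for instance because they became unfit): shift = +100 to +200 steps.
- u equal in both arms with the same selection: shift = 0.

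**5. Cross-check with a selection model.** Suppose propensity for surgery is a normal latent variable, with less active people more likely to be operated on, and r the strength of its correlation with steps. With a proportion p operated on and q the normal quantile of p, the operated mean shifts by −r × SD × φ(q)/p. With no true effect, SD 2142 and r from 0.2 to 0.5:

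| Operated, control / intervention | Shift in steps | % of 1200 |
|---|---|---|
| 95% / 95% | 0 | 0 |
| 95% / 90% | −37 to −93 | 3 to 8 |
| 90% / 80% | −66 to −166 | 6 to 14 |
| 95% / 85% | −71 to −177 | 6 to 15 |
| 90% / 70% | −129 to −323 | 11 to 27 |

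Reversing the sign of the correlation gives the operated group the higher mean, so the shift becomes positive.

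**6. Precision at test 3.** Power = Φ(1200 / (2142 × √(2/n)) − 1.960). Start from 55 per arm, remove 10% for withdrawal (49.5), then keep only those operated on, with the same share in both arms:

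| Share operated | n per arm | Power |
|---|---|---|
| 100% | 49.5 | 0.80 |
| 95% | 47.0 | 0.78 |
| 90% | 44.6 | 0.75 |
| 80% | 39.6 | 0.70 |
| 70% | 34.6 | 0.65 |

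**7. Spill-over to test 2.** Test 2 has a value whether or not surgery follows. A repeated-measures ANCOVA that uses only participants with all three tests would nevertheless remove non-operated people from the test 2 comparison. A mixed model fitted to all available visits would keep them at test 2. At test 3 it would supply an implied post-surgery value under missing-at-random, a quantity the article does not define.

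**The case against.** The best defence has four parts.

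- *The plan foresees missing follow-up and keeps allocation, and details belong in an analysis plan that is not shown.* This stands for missing-data methods and visit windows. It does not reach the visit schedule, which is fixed here: an analysis plan cannot recover an assessment that was never scheduled.
- *Test 2 already gives a comparison timed from baseline on every primary and secondary outcome.* This stands, and it limits the point to test 3 plus the spill-over in step 7.
- *Nothing in the documents says the programme changes who is operated on.* Also true. Participants are already listed for surgery and no cancellation rate is given. A reader might infer that the programme diverts its best responders from surgery; that is only a plausible consequence of its aims.
- *The direction is open.* This stands. A reader might infer that test 3 is biased against the programme. That follows only if those not operated on walk more than the rest and are more frequent in the intervention arm. If they left the list because they became unfit, the sign could reverse.

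It may also be said that recovery after surgery is the intended question. It is a reasonable one, but it is conditional on surgery and should carry that label.

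**Conclusion.** The point holds for test 3. If any participant goes without surgery during the trial, that person has no test 3 value to analyse. The intention-to-treat promise and the all-time-points hypothesis then cannot be met at that visit, which compares operated participants only. This rests on the schedule alone and on no assumed rate.

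The size and sign of any bias are unknown. With equal surgery rates and the same selection in both arms the bias is zero, although the comparison still describes operated participants only. Under the assumed inequalities above, it runs from a few per cent to about a quarter of the 1200-step target, in either direction.

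A reader might go further and conclude that the whole trial is not intention-to-treat. The documents do not support that: test 2 is defined for everyone randomised and is unaffected by this definition, provided the analysis does not require a test 3 value.

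**What to change.** The article reports the trial as ongoing, so the following can be set by amendment before any comparison by arm:

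1. Make test 2 the primary intention-to-treat comparison, analysed so that a missing test 3 does not remove a participant.
2. Label the post-surgery test 3 contrast as supportive and conditional on surgery, and limit the all-time-points hypothesis to match.
3. Report by arm the proportion operated on and the time from randomisation to surgery.
4. For participants without surgery by a prespecified time from randomisation, schedule a last assessment at a fixed time, so that a late comparison of everyone randomised exists. Do not adjust that comparison for time since randomisation: for operated participants this is time to surgery plus 26 weeks, which the programme might itself affect.

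The cost is a schedule amendment and one late assessment for those not operated on, probably few. The late comparison will mix operated and non-operated people, so it answers a different question from recovery after surgery; the supportive contrast in item 2 keeps that question available. If nearly everyone is operated on, the change costs almost nothing and item 3 will show it.

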**Discussion:**

This study seeks to address a significant gap in current osteoarthritis management practice by providing evidence for the effectiveness of an exercise programme combined with behaviour counselling for adults waiting for hip and knee arthroplasty. Theory-driven evidence-based strategies that can improve an individual’s exercise self-efficacy and self-management capacity could have a significant impact on the development of secondary chronic disease in this population. Information gained from this study will contribute to the evidence base on the management of adults waiting for hip and knee arthroplasty.

**Trial registration:**

Australian New Zealand Clinical Trials Registry, ACTRN12617000357358. Registered on 8 March 2017.

**Electronic supplementary material:**

The online version of this article (10.1186/s13063-018-2808-z) contains supplementary material, which is available to authorized users.

## Background

Osteoarthritis (OA) is a common musculoskeletal problem, which affects over 40% of adults over the age of 70 years [1] and is associated with substantial pain and disability [2]. Patients with advanced OA of the hip or knee are often referred for surgery to replace the affected joints. Internationally, the waiting time for surgery varies from 6 to 12 months [3]. Due to pain, physical activity levels in patients with OA are substantially lower than levels in non-arthritic older people [4]. The prolonged periods of reduced physical activity during the wait for elective surgery significantly increase the risk of developing other major health problems, such as cardiovascular and metabolic diseases [5]. Inactivity may exacerbate physical impairments, such as muscle weakness, resulting in an increased rate of functional decline [6] and reduced rate of recovery post-surgery. In contrast, substantial research supports the benefits of regular physical activity in the prevention and treatment of chronic medical conditions including OA [7, 8] at all stages of the disease.

Previous research has largely concentrated on the effects of pre-operative exercise on post-operative pain and mobility [9]. Despite small improvements of 10% in physical activity after joint replacement, activity remains much lower than in healthy people [10]. The reason for this is unknown but may be because patients’ adherence to exercise tends to drop over time [11] and clinicians often do not appreciate and promote exercise as a treatment option [12]. Consequently, the immediate small positive benefits in pain and mobility are not sustained, as participants are not adequately supported to maintain exercise levels once the intervention finishes. An individualised intervention programme with a counselling component may address the challenge of achieving prolonged increases in physical activity for patients with OA.

Physical activity interventions based on social psychological theory are more effective than atheoretical ones in promoting health-protective behaviour [13]. In addition, interventions are more cost-effective when they have theoretically devised approaches and clearly measurable constructs. A theoretical basis for the intervention components and inclusion of key psychological measures based on theory can demonstrate *how* the intervention works, highlighting the processes by which behaviour change occurs [14]. The Health Action Process Approach (HAPA) [15] stipulates a dual-phase approach to action: a *motivational* phase (i.e. outcome expectancy, risk perception, action self-efficacy and intention) and a *volitional* phase (i.e. maintenance self-efficacy, recovery self-efficacy, action planning, coping planning and action control). According to HAPA, intention is a necessary but insufficient condition for action initiation and persistence. People also need to identify effective volitional self-regulatory strategies to enact their intentions and prevent relapse. The effectiveness of HAPA-based interventions has been demonstrated in multiple populations and contexts and across multiple health behaviours [15–21]. The use of this framework to promote physical activity in people with OA does not appear in the literature. However, HAPA has recently been used to identify six physical activity attributes that are most salient to adults with knee OA [22], which supports this framework in this population.

This report describes the methodology of the ENHANCE trial, a randomised controlled trial to test the effectiveness of the ENHANCE programme for a usual care control group. This study seeks to test the hypothesis that the combination of a targeted exercise prescription with behaviour change counselling based on HAPA will be more effective than usual care in increasing the number of daily steps at all-time points after intervention. Concurrently less pain, improved function and reduced metabolic and cardiovascular risks factors will be recorded.

